##### Megastudy interventions

The study will have 11 different intervention arms, of which 10 are low-cost messaging interventions and one is a small financial incentive intervention (see Table 1), and a standard care control arm. At the baseline visit, immediately after randomization, all participants assigned to one of the 10 messaging intervention arms will be shown a brief (1–2 min) avatar video message encouraging them to return for a repeat HIV test in 3 to 6 months (see Fig. 1).

**Table 1 Tab1:** Megastudy interventions

Intervention	Underlying barrier and intervention rationale	Intervention content
Risk assessment	• Barrier: Low perceived HIV risk (particularly after an HIV-negative test) can be a barrier to retesting • Rationale: Prompting a self-evaluation of HIV risk can make specific risk factors more salient to participants	Brief video message about risk assessment at baseline; 2 SMS messages at 8 and 11 weeks
U = U messaging	• Barrier: Inaccurate mental models such as beliefs that one only needs an HIV test if they have symptoms, or that HIV treatment does not reduce risk of HIV transmission, can be barriers to HIV retesting • Rationale: Updating mental models with new information on asymptomatic HIV infection and modern ART (“Undetectable = Untransmittable” U = U) [33]	Brief video message about U = U messaging at baseline; 2 SMS messages at 8 and 11 weeks
Community benefits	• Barrier: Decreased salience of preventive behaviors over time can be a barrier to retesting • Rationale: Messaging that emphasizes benefits of HIV testing to one’s community can leverage altruism and thereby increase salience of engaging in preventive behaviors like retesting	Brief video message about community benefits at baseline; 2 SMS messages at 8 and 11 weeks
Fresh start effect	• Barrier: Decreased salience of preventive behaviors over time can be a barrier to HIV retesting • Rationale: “Fresh start” effect can be used to motivate health behaviors at a specific time (such as the time of a baseline, negative HIV test) [34]	Brief video message about fresh start at baseline; 2 SMS messages at 8 and 11 weeks
Standard health education about HIV	• Barrier: Lack of knowledge about basic HIV fact or belief in myths [35] • Rationale: Providing correct information about HIV is a standard public health approach and may increase understanding of the benefits of HIV retesting	Brief video message about basic HIV facts at baseline; 2 SMS messages at 8 and 11 weeks
Default appointment	• Barrier: Decreased salience of preventive behaviors over time • Rationale: Setting a default appointment time for retesting can leverage status quo bias [36] and overcome decreased salience of HIV retesting over time	Brief video message with a default appointment date at baseline; 2 SMS messages at 8 and 11 weeks
Reserved for you	• Barrier: Competing priorities can be a barrier to HIV retesting • Rationale: A message indicating that the HIV test is “reserved for you” can leverage scarcity, implied exclusivity, and loss aversion to counter this barrier [37]	Brief video message about reserved for you test kit at baseline; 2 SMS messages at 8 and 11 weeks
Social norms (default avatar)	• Barrier: Internalized or anticipated stigma can be a barrier to HIV retesting • Rationale: Messages that frame HIV testing as a prevailing social norm [38] may reduce internalized or anticipated stigma	Brief video message about social norms at baseline with default avatar (male, ~30 years); 2 SMS messages at 8 and 11 weeks
Social norms (matched avatar)	• Barrier: Internalized or anticipated stigma can be a barrier to HIV retesting • Rationale: Messages that come from a peer may be more persuasive than those delivered by someone outside of one’s peer group and framing HIV retesting as a prevailing social norm may reduce internalized or anticipated stigma	Brief video message about social norms at baseline with avatar matched to participant’s sex and age group; 2 SMS messages at 8 and 11 weeks
Empowerment/goal-setting	• Barrier: Decreased salience of preventive behaviors over time and competing priorities can be barriers to HIV retesting • Rationale: Engaging participants in goal-setting may make retesting more salient and overcome self-control problems [39]	Brief video message about empowerment and goal-setting at baseline; 2 SMS messages at 8 and 11 weeks
Financial incentive	• Barrier: The real and perceived costs of HIV testing, including cost of transportation and time taken can be barriers to retesting • Rationale: Financial incentives can offset the costs associated with retesting and also serve as an immediate benefit to some participants	Counselor tells participant at baseline that they will receive a small financial incentive (< USD $5) if they return for retesting in 3–6 months. Disbursement of financial incentive at 3–6 months retesting visit
SOC (control)		SOC MoH post-test counseling procedures

**Fig. 1 Fig1:**
[figure not shown]
Schematic for the IBIS megastudy of interventions to promote HIV retesting among adults at increased risk of HIV infection in western Kenya and southwestern Uganda

The specific message content and framing will differ based on the participant’s randomization assignment. For example, participants who have been assigned to the “HIV risk assessment” study arm will be shown a video that asks them to reflect on several specific HIV risk factors and whether they have recently engaged in any of those activities, before prompting them to return for another test. Nine of the 10 messaging arms will have the same default avatar face for consistency. Based on feedback from the local adaptation phase, a male avatar of approximately 30 years of age was selected as the default. The “social norms (matched avatar)” study arm will use an avatar face that is matched to the participant’s age (≤ 30 years/> 30 years) and sex (male/female); the message content will be the same as that for the “social norms (default avatar)” study arm.

Participants who have been assigned to one of the 10 messaging arms will also receive brief SMS follow-up messages at 8 weeks and 11 weeks after their baseline visit, reminding them to return for HIV retesting in the 3–6-month window post-enrollment. The content of these SMS messages will also be aligned with the core content categories to which participants are assigned.

Participants who are assigned to the financial incentive study arm will be told by their HIV test counselor at baseline that they will receive a small financial incentive (< US$5) if they return for another HIV test within 3 to 6 months; they will not be shown any video messaging or receive follow-up SMS reminders. Participants in all study arms, including the control, will receive standard of care HIV post-testing counseling from HIV test counselors.

#### Participant timeline and procedures

Immediately following enrollment, participants will complete a brief baseline survey including questions on demographics and recent HIV risk factors. Following the baseline survey, they will be randomized to one of the 12 study arms and, if assigned to one of the 10 messaging intervention arms, they will be shown the associated baseline video message. The study software will be programmed to automatically show only the video message for the study arm to which the participant has been randomized, to reduce possible human error. All participants will be reminded to return for another HIV test 3 to 6 months after the baseline visit. Participants who return for a repeat HIV test at follow-up will receive standard HTS through the hospital or clinic and will complete a brief follow-up study survey to assess HIV risk factors since baseline enrollment. The study team will record HIV test results as well. Participants who have been assigned to the incentive arm and return for retesting at follow-up will receive a small financial incentive (up to $5 USD) at the time of retesting. The schedule of study enrollment, interventions, and assessments is detailed in Table 2. Participants may seek and receive any concomitant care during their participation in this trial.

**Table 2 Tab2:** SPIRIT figure: schedule of enrollment, allocation, interventions, and assessments in the IBIS megastudy

	Enrollment	Post-allocation		Close-out	Post-close out
Timepoint	Baseline	*t* + 8 weeks	*t* + 11 weeks	*t* + 12 weeks–*t* + 24 weeks	*t* + 25 weeks–*t* + 48 weeks
Enrollment:					
HIV testing*	X			X	
Eligibility screen	X				
Verbal consent	X				
Allocation	X				
Interventions:					
[Control arm]	X				
[Incentive arm]	X			X	
[Messaging arms, *n* = 10]	X	X	X		
Assessments:					
Questionnaire	X			X	
Post-follow up survey for non retesters**					X

^*^ HIV testing is conducted per Ministry of Health (MoH) standard of care and is not a study procedure; HIV test results will be documented on study case report forms (CRFs)

^**^ We will reach out to a small sample of participants who did not return for HIV retesting to see if they tested elsewhere and, if not, to ask about their reasons for not retesting

#### Outcomes

The primary outcome will be HIV retesting at any study venue 3–6 months after the initial baseline HIV test. We will use either participant demographic information (such as name, phone number, birthdate) and/or national identification number or electronic medical record number (if available) at baseline and time of retesting to verify participant identity (using procedures we have used in prior studies [5, 40]) and measure HIV retesting.

The secondary outcome will be PrEP referral acceptance (i.e., willingness to be referred to the PrEP clinic) among participants who retest HIV-negative and are not taking PrEP at time of retesting. We will measure acceptance of referral to PrEP services at time of retesting. Other outcomes will include the proportion of persons who test HIV positive (i.e., seroconvert) among participants who retest for HIV, as well as linkage to care and ART-initiation among those who seroconvert.

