### Sample size

We made the following assumptions in determining the sample size and minimum detectable effect sizes. With 64,000 adults (≥ 15 years) testing for HIV in 2023 at the eight study HIV testing service sites and a reported HIV positivity of ~ 2%, we estimate there are about 62,700 HIV-negative adults tested per year in these study communities. We estimate that about 50% of adults (about 31,000/year) accessing HIV testing at HIV clinic sites will be classified as being at increased risk of HIV infection based on their self-reported answers to risk screening questions and thus will require quarterly HIV retesting. Based on our prior HIV retesting studies in Uganda, we anticipate at least 90% of eligible adults will agree to participate in the megatrial [29, 32]. With enrollment over 18–24 months, we anticipate enrolling 30,000–40,000 participants in the trial, with a range of 2500–3333 participants per arm in a 12-arm trial.

Based on our previous retesting study in Uganda, we assumed that 38% of the control group will retest for HIV within 6 months [29]). With a sample size of at least 3000 participants/arm, we will have 80% power to detect a 4.7 percentage-point difference in HIV testing for any of the intervention groups compared to the control group. These power calculations account for multiple hypothesis testing by using a Bonferroni correction and setting the significance level to 0.00455 (i.e., 0.05/11 comparisons between interventions and control). This is a very conservative approach; however, since we will have more statistical power in our analyses by using the Benjamini and Hochberg Procedure to control the false discovery rate [41] and covariate adjustment will also improve efficiency. Thus, in practice we expect to be able to detect differences between each intervention group and the control group that are smaller than 4.7%.

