### Statistical analysis

For the primary outcome of HIV retesting, we will estimate a logistic regression model to determine the effect of each behavioral intervention. The main predictors in our regression model will be indicator variables for each intervention group, with the reference being the control group. We will also include study site fixed effects to account for variation between study sites in HIV retesting. While the inclusion of site fixed effects can reduce power by consuming degrees of freedom, it can also increase precision when there is substantial variation in retesting rates across sites. Given the number of intervention groups, we will account for multiple hypothesis testing by using the Benjamini and Hochberg Procedure to control the false discovery rate [41].

For secondary analyses, we will determine the effect of the interventions relative to control on PrEP uptake (i.e., acceptance of referral to PrEP) at time of retesting HIV-negative by estimating a logistic regression model where the dependent outcome is PrEP uptake, with the model including fixed effects for study community and adjusting for multiple comparisons as described for the primary outcome. We will conduct similar analyses with logistic regression models for the dependent outcomes of HIV seroconversion among participants who retest and linkage to HIV care and ART initiation among those who test HIV-positive. We will report the proportion of participants who retest HIV antibody-positive by study arm and overall, as well as the proportion who link to HIV care and start ART among persons who seroconvert. Although we will be underpowered to detect differences between study arms in HIV-positivity and linkage to care, we will be able to describe these important outcomes among a large sample of adults at risk of HIV exposure and we will identify baseline characteristics that are associated with incident HIV infection using logistic regression models.

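### PrEP referral acceptance is compared between arms only among people who retest, so the contrast is not randomised and should not be tested as an intervention effect

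*Protocol article*

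**What the plan says.** The Outcomes section names one secondary outcome: "The secondary outcome will be PrEP referral acceptance (i.e., willingness to be referred to the PrEP clinic) among participants who retest HIV-negative". The full restriction is to acceptance "among participants who retest HIV-negative and are not taking PrEP at time of retesting". Measurement happens at that visit only: "We will measure acceptance of referral to PrEP services at time of retesting".

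The same section gives the primary outcome: "The primary outcome will be HIV retesting at any study venue 3–6 months after the initial baseline HIV test". Entry to the secondary denominator therefore requires success on the primary outcome.

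The Statistical analysis section states that "we will determine the effect of the interventions relative to control on PrEP uptake". It does so by logistic regression, "with the model including fixed effects for study community and adjusting for multiple comparisons as described for the primary outcome". It plans similar models for seroconversion among those who retest. Its one caveat is low power for HIV-positivity and linkage to care. Selection into retesting is not mentioned.

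**The concern.** Retesting, an HIV-negative result and PrEP use at the retest visit are all determined after randomisation. If an arm raises retesting, its retesters include people whose counterparts in the control arm stayed away. Those extra people may be more or less willing to accept a PrEP referral than people who would have come back anyway. The arms would then differ in acceptance even if no message changed anyone's willingness. Site or community fixed effects and multiplicity control do not address this, because neither acts on who enters the denominator.

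At stake is the reading of the only named secondary outcome. An arm could be reported as lowering or raising PrEP acceptance when it only changed who returned. It could look worse than control on this outcome while producing more accepted referrals.

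**Working it through.** **Inputs from the protocol article (Sample size).** Control retesting: "we assumed that 38% of the control group will retest for HIV within 6 months". Detectable difference 4.7 points, so 38.0% versus 42.7%; 3000 per arm; 80% power; significance level 0.05/11.

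**Assumptions, because the article gives no figures.** Willingness to accept referral, its association with retesting, and any uplift other than 4.7 points. Removal of HIV-positive participants and PrEP users from the denominator is ignored.

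**Step 1: the plan's own figure.** 0.05/11 = 0.004545. A two-sided comparison of 38.0% with 42.7% at 3000 per arm (pooled variance) has 80.9% power, and the minimum detectable difference is 4.66 points. The stated 80% and 4.7 points reproduce. No figure is given for the PrEP outcome.

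**Step 2: who is compared.** Control retesters: 3000 × 0.38 = 1140. Intervention retesters: 3000 × 0.427 = 1281. The 141 extra are 141/1281 = 11% of the intervention group and have no counterpart among control retesters.

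**Step 3: direction.** Let *a* be acceptance in people who would retest anyway, *b* acceptance in the extra retesters, and *u* the uplift. With willingness unchanged, control acceptance is *a* and intervention acceptance is (0.38*a* + *ub*)/(0.38 + *u*). With *u* = 0.047:

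- *a* = 50%, *b* = 30%: (0.1900 + 0.0141)/0.427 = 47.8%, a shift of -2.2 points. Accepted referrals per 3000 are 570 in control and 612 in intervention.
- *a* = *b*: no shift.
- *a* = 30%, *b* = 50%: (0.1140 + 0.0235)/0.427 = 32.2%, a shift of +2.2 points.

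**Step 4: size across a range.** Let R be a standard normal retesting propensity and W a standard normal willingness, with correlation ρ. A person retests if R > c and would accept if W > t. The cut-off c is set to each arm's retest rate, and t to population willingness of 30% or 50%, the same in both arms. Acceptance among retesters is P(W > t | R > c). Accepted referrals per person randomised are P(W > t, R > c). The rejection probability is that of a two-sided z-test of the conditional proportions, with 3000 × retest rate per arm.

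| Retesting, control vs intervention | ρ | Shift among retesters (points) | Rejects at 0.05 | Rejects at 0.05/11 | Accepted referrals per person randomised (points) |
|---|---|---|---|---|---|
| 38% vs 42.7% (protocol) | 0.4 | about -1.4 | about 11% | 1.6% | within the range below |
| 38% vs 42.7% (protocol) | 0.2 to 0.6 | -0.6 to -2.3 | 6 to 21% | 1 to 5% | +1.5 to +2.7 |
| 38% vs 50% (assumed) | 0.4 | -3.3 to -3.4 | 41 to 42% | 13 to 14% | +3.7 to +6.3 |
| 38% vs 50% (assumed) | 0.2 to 0.6 | -1.5 to -5.7 | 13 to 83% | 2 to 53% | +3.5 to +6.5 |

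A valid test would reject at 5% and about 0.45% in the two rejection columns. The Benjamini-Hochberg rule that the plan adopts works between these two thresholds. The shifts are negative only because ρ was taken as positive; a negative ρ reverses their sign.

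**The case against.** **Size.** At the protocol's own design difference the distortion is modest: at a correlation of 0.4, about -1.4 points, with 1.6% rejection at 0.05/11. Large rejection rates need an uplift the article never states, a strong correlation and no multiplicity adjustment. This stands, and the design-effect figures should lead. The article does say that incentives raised retesting in an earlier trial, without giving the size, so a larger uplift in that arm is plausible but unquantified.

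**Direction.** A reader might infer that an effective arm draws in less motivated people, so that the best arm will look harmful. Nothing in the document supports a direction. The risk-assessment arm, for instance, targets low perceived risk and could bring back people more interested in PrEP.

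**Denominator.** A reader might see a contradiction because the Statistical analysis section does not repeat the not-on-PrEP restriction. It analyses an outcome already defined under Outcomes, and the shorter wording names no different population.

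**PrEP users.** A reader might also say that excluding people on PrEP at retest discards successes. The outcome is acceptance of a referral, which people already on PrEP do not need. What remains is only that this status, too, is determined after randomisation.

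**Different questions.** The conditional proportion is a sensible description of the care cascade, and an all-randomised endpoint cannot isolate an effect on willingness. Both are true, and they support reporting both quantities. They do not make the conditional contrast a treatment effect.

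**Unseen analysis plan.** It could add an all-randomised analysis. The point, however, concerns what the article does state: this denominator, tested and described as an effect.

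**Conclusion.** The point holds. The only named secondary outcome conditions on the trial's primary outcome, and its arm contrasts are tested and worded as intervention effects. They are not protected by randomisation and can be biased upward, downward or not at all.

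Under the stated assumptions (no effect on willingness, positive correlation of 0.2 to 0.6), the spurious shift at the protocol's design difference is 0.6 to 2.3 points. It is 1.5 to 5.7 points if an arm brings retesting to an assumed 50%. In every scenario tabulated, the conditional proportion falls while accepted referrals per person randomised rise.

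The documents do not show that bias will occur in a given direction, that the trial will report false harm, or that its main conclusions are at risk. The primary outcome, its power and its analysis are untouched. Should-fix is the proportionate grade.

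**What to change.** - **Tested endpoint.** Among all randomised participants, score 1 for retesting HIV-negative in the 3–6-month window and accepting PrEP referral, and 0 otherwise. Use the primary outcome's model and multiplicity rule.
- **PrEP users.** Do not score being on PrEP at retest as a success. The Eligibility criteria do not exclude PrEP users at baseline, so that would credit pre-existing use.
- **Conditional proportion.** Report acceptance among eligible retesters by arm, beside the tested endpoint, as description, without a test and without the word effect.
- **Seroconversion among retesters.** Treat it the same way. The existing caveat about HIV-positivity concerns power, not selection.

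**Cost.** A wording change to the endpoint and its analysis. The two components, retesting and referral acceptance at the retest visit, are already to be recorded. Follow-up is expected to run to December 2027, and the investigators and statistician are to stay blinded through the primary analysis, so the change can be made before arm-level results are seen.

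**Downside.** The new endpoint mixes the retesting effect with acceptance, and can rise with no change in willingness, which is why the conditional proportion stays on display. Power may also be limited. In the first example of Step 3 (19.0% versus 20.4% of all randomised), it is 28% at 0.05 and 7% at 0.05/11.

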### Sample size

We made the following assumptions in determining the sample size and minimum detectable effect sizes. With 64,000 adults (≥ 15 years) testing for HIV in 2023 at the eight study HIV testing service sites and a reported HIV positivity of ~ 2%, we estimate there are about 62,700 HIV-negative adults tested per year in these study communities. We estimate that about 50% of adults (about 31,000/year) accessing HIV testing at HIV clinic sites will be classified as being at increased risk of HIV infection based on their self-reported answers to risk screening questions and thus will require quarterly HIV retesting. Based on our prior HIV retesting studies in Uganda, we anticipate at least 90% of eligible adults will agree to participate in the megatrial [29, 32]. With enrollment over 18–24 months, we anticipate enrolling 30,000–40,000 participants in the trial, with a range of 2500–3333 participants per arm in a 12-arm trial.

Based on our previous retesting study in Uganda, we assumed that 38% of the control group will retest for HIV within 6 months [29]). With a sample size of at least 3000 participants/arm, we will have 80% power to detect a 4.7 percentage-point difference in HIV testing for any of the intervention groups compared to the control group. These power calculations account for multiple hypothesis testing by using a Bonferroni correction and setting the significance level to 0.00455 (i.e., 0.05/11 comparisons between interventions and control). This is a very conservative approach; however, since we will have more statistical power in our analyses by using the Benjamini and Hochberg Procedure to control the false discovery rate [41] and covariate adjustment will also improve efficiency. Thus, in practice we expect to be able to detect differences between each intervention group and the control group that are smaller than 4.7%.

